## Abstract

**Background:**

Autistic children experience disproportionately high rates of malnutrition compared to non-autistic (NA) peers. Sensorimotor integration differences (SMD), prevalent in 69–95% of autistic individuals, are hypothesized to drive this disparity. SMD contributes to core autistic traits that exacerbate feeding difficulties (e.g., food selectivity), potentially leading to malnutrition and gut dysbiosis. Current caregiver-reported SMD assessments lack validity in autistic populations and are prone to cultural and socioeconomic biases, limiting insight into nutritional outcomes.

**Objective:**

To investigate relationships between objectively measured SMD, dietary patterns, nutritional status, and gut microbiota composition in autistic children versus NA peers.

**Methods:**

This comparative cross-sectional study will recruit 100 autistic children and adolescents (aged 3–17 years) and 200 age-/sex-matched NA peers (including 100 with developmental disorders other than autism). Autism severity will be assessed using the Childhood Autism Rating Scale; NA peers will be screened with the Autism Spectrum Quotient-10. Dietary intake will be evaluated via three 24-hour dietary recalls, supplemented by questionnaires on socioeconomic status, health, and medications. Nutritional status (anthropometry, bioimpedance) and gut microbiota composition and diversity will be assessed. SMD proxies (sensory gating, sensory adaptation) will be measured using a smartphone application.

**Analysis:**

Group comparisons will employ multivariate regression models, adjusting for age, sex, socioeconomic status and medication use. We hypothesize significant between-group differences in dietary patterns, nutritional status, microbiota profiles, and SMD measures. Objectively measured SMD in autistic children and adolescents is expected to correlate with symptom severity, dietary patterns, and differences in microbiota composition and diversity.

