### Study design and context

2.1

The present document outlines the research protocol for an analytical observational, comparative cross-sectional study. The study will be conducted in the cities of Quito and Riobamba, which are located in the Highlands of Ecuador. Data collection is planned to start in the fourth trimester of 2025 and end the fourth trimester of 2026. Data analysis is planned to start in the first trimester of 2026 and end the fourth trimester of 2028. A pilot study involving 10 autistic and NA children will be conducted during the third trimester of 2025 to refine procedures and instruments. The overall study design and procedures are summarized in **Supplementary Figure 1**.

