### Recruitment and patient involvement

2.3

This study protocol was designed in collaboration with a special education school in Quito and a child neurodevelopment center in Riobamba. Both are private centers where autistic children and adolescents receive rehabilitation services. Additional participants will be recruited through posters and flyers distributed on social networks, at educational institutions, and through associations of autistic children’s parents. Children in Group B will be recruited from the family networks of Group A participants and matched for sex and age with their autistic peers. The target ratio between Groups A and B is approximately 1:2. During the development of the protocol, parents and professionals from recruitment sites provided valuable recommendations about the recruitment process, procedures and study goal.

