### Procedures

2.4

Data will be collected through three ~60-minute visits conducted at participants’ homes or preferred locations by trained researchers (including medical professionals). All personnel will receive standardized training in instrument administration, pediatric assessment protocols, and transcription procedures. A summary of visits is depicted in **Table 1**.

**Table 1 T1:** Summary of study visits and procedures.

Visit	Procedures conducted	Measurements/tools used
Visit 1	- Informed consent - Sociodemographic/clinical data - First dietary assessment - Autism screening - Handing out stool sample collection kits	- Questionnaires - CARS (group A) - POSI/AQ-10 (all groups) - 24-HDR
Visit 2	- First neurobehavioral assessment - Anthropometry/bioimpedance - First dietary assessment	- Smartphone application - Stadiometer, InBody120 - 24-HDR
Visit 3	- Second neurobehavioral assessment - First dietary assessment - Stool sample collection - Completion of pending data	- Smartphone application - 24-HDR

24HDR, 24-hour dietary recall; AQ-10, 10-item Autism Spectrum Quotient; CARS, Childhood Autism Rating Scale; POSI, Parent’s Observations of Social Interactions.

The following data will be collected:

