#### Analysis of the relation between exposures and outcomes

3.6.2

In all analyses, the researchers will blind the identity of the comparison groups. Statistical analysis will be performed using multilevel mixed-effects linear and nonlinear models in R Studio and Python (56). These models offer several advantages over standard parametric and non-parametric tests: they are more robust to violations of normality, which is common in biological data, and they do not require homoscedasticity (57, 58). Additionally, they accommodate the nested structure of our data (trials nested within sessions, sessions nested within participants, participants nested within groups) and handle missing data more effectively than repeated-measures ANOVA. Normality of residuals will be assessed visually with quantile-quantile (Q-Q) plots and statistically using the Shapiro–Wilk test; homoscedasticity will be evaluated with the Breusch–Pagan test (59, 60). Data will be considered statistically significant at a p-value < 0.05. Given the large number of variables related to diet, nutritional status, ASD severity, and sensorimotor integration, exploratory analyses will include the Kruskal–Wallis test to compare groups on non-normally distributed variables (61). In addition, cluster analysis (k-means clustering and equivalent algorithms) will be used to identify profiles of gut microbiota or dietary patterns (62).

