### Ethics

3.7

This study protocol was approved by the Committee on Ethics in Human Research (CEISH) at the Escuela Superior Politécnica de Chimborazo (Ref No: IO-01-CEISH-ESPOCH-2025). The study will be conducted in accordance with the principles of the Declaration of Helsinki.

Prior to participation in “Proyecto Wiñay”, written informed consent will be obtained from the parents, guardians, or legal representatives of the children (see Annex 13 in the **Supplementary Material**). In cases where a non-emancipated minor lives under the care of grandparents, one grandparent serving as the legal guardian may provide consent. Adolescents aged 15 years or older will provide informed assent using a form written in simple language (Annex 14). To facilitate communication with children of varying abilities, an assent document with pictograms has been developed (Annex 15). All participants and their guardians will receive a comprehensive explanation of the project’s objectives, potential risks and benefits, methodologies, expected outcomes, and data usage policies. These explanations will be delivered in clear, simple language to ensure full comprehension. Furthermore, a commitment to transparent, community-centered, and timely communication will be upheld throughout the research process to maintain respect for all participants. Both parents and children will be explicitly informed of their right to withdraw from the study at any time without any negative consequences.

Data collection will occur in a comfortable and respectful environment, prioritizing the sensitivity of the children and their families. Where possible, sessions will be conducted in the participant’s home to minimize distress. Caregivers will be empowered to specify conditions necessary for their child’s comfort and well-being, and our team will accommodate these preferences. All data will be collected by personnel trained to work with neurodivergent children. Respect for participants will be upheld through the use of appropriate language, strictly avoiding derogatory, stigmatizing, discriminatory, obsolete, or incorrect terminology, following established best-practice guidelines (63). It is important to emphasize that the data collection methods are non-invasive and pose no risk of harm or injury to participants.

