### “Proyecto Wiñay” in the current Ecuadorian context

4.1

Feeding challenges in autistic individuals pose significant health concerns, particularly due to their impact on nutritional status (67, 68). SMD constitutes a key contributor to these challenges, yet its association with dietary patterns and GM characteristics remains unexplored in the Ecuadorian pediatric population. Our study aims to fill this gap by conducting an integrated assessment of SMD, dietary patterns, and GM characteristics in autistic children from the Andes, a group known to face high malnutrition rates and limited healthcare access (24). While other studies acknowledge the link between SMD and malnutrition in autism, our approach is distinct in its specific adaptation of methodologies to the Ecuadorian context. We hypothesize that SMD contributes to restrictive diets that subsequently alter GM composition and diversity, potentially exacerbating core autistic symptoms and perpetuating a cycle of malnutrition.

This research employs innovative techniques, including neurometrics to objectively assess SMD through measures of sensory gating and habituation as well as general motor behaviors. Additionally, GM characteristics will be evaluated in a population with high prevalence of intestinal parasitosis, a factor often overlooked in studies from high-income countries (69). Further, we will use WHO-standardized anthropometric measurements to assess three groups: autistic children, NA children, and children with developmental disorders other than autism. This comparative approach will provide valuable insights into the unique nutritional challenges and GM alterations specifically associated with autism.

Unlike previous Ecuadorian studies (e.g., Zurita et al., 2020), which focused primarily on nutritional status and GM, “Proyecto Wiñay” offers a more comprehensive approach by incorporating objective SMD analysis (70). Furthermore, our study will recruit a larger sample size from a more ethnically diverse population (including participants from both Quito and Riobamba cities) and across a broader age range. Although cross-sectional, our study has the potential to establish the basis for future longitudinal studies tracking GM changes or symptom severity linked to sensorimotor-mediated dietary patterns.

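### City (Quito or Riobamba) is missing from the stated covariates and the matching rule, so it can confound contrasts involving Group C; session place and accommodations should be recorded for sensitivity analysis only

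*Protocol article*

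**What the plan says.** **Cities.** Section 2.1 states: "The study will be conducted in the cities of Quito and Riobamba". Section 2.3 names the collaborating centres as "a special education school in Quito and a child neurodevelopment center in Riobamba", and adds social networks, schools and parent associations as further sources without assigning them to a group. Section 4.1 counts the two cities among the study's strengths: "a more ethnically diverse population (including participants from both Quito and Riobamba cities".

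**Groups.** Section 2.3 draws Group B from the family networks of Group A and matches on sex and age. The abstract calls all 200 non-autistic children age- and sex-matched. Section 2.2.3 defines Group C by diagnosis and gives neither a recruitment source nor a city distribution.

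**Models.** The abstract fixes the adjustment: "Group comparisons will employ multivariate regression models, adjusting for age, sex, socioeconomic status and medication use". Section 4.2 repeats the same four variables as examples, promises unspecified sensitivity analyses, and names medication use as a covariate in the alpha-diversity models and in PERMANOVA. Section 3.6.2 gives the data structure as "trials nested within sessions, sessions nested within participants, participants nested within groups".

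**Test setting.** Under section 2.4, visits are "conducted at participants’ homes or preferred locations by trained researchers". Section 3.7 prefers the home where possible and adds: "Caregivers will be empowered to specify conditions necessary for their child’s comfort and well-being, and our team will accommodate these preferences".

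**The concern.** City is a plausible common cause of diet, body size and gut microbiota, and the authors themselves treat the two city populations as adding diversity. If Group C is recruited in a different Quito-to-Riobamba proportion from Group A, part of any A-versus-C difference is a difference between cities. The same holds, diluted, when B and C are pooled. Group C is there to show what is specific to autism rather than to developmental disorders in general, so this is the contrast in which an unadjusted city effect would mislead most.

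A second and separate matter is the neurobehavioural test. Place and surroundings may vary from child to child, and requests for accommodation may be unevenly spread over the groups. If nothing is recorded at the session, nobody can later check whether the startle and behaviour results depend on setting.

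**Working it through.** **1. The plan's own figure.** Section 2.2.4 uses p1 = 0.57 (Group A), p2 = 0.37 (Group B), Z values 1.96 and 0.84:

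n = (1.96 + 0.84)² × [0.57 × 0.43 + 0.37 × 0.63] / 0.20² = 7.84 × 0.4782 / 0.04 = 93.7, so 94 per group. Then 94 / 0.95 = 98.9, so 99, which the plan rounds to 100. The figure reproduces. The 20-point difference behind it is for A versus B only; the article states no design difference for A versus C.

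**2. Where city could enter the stated plan.**

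| Place in the article | What it lists | City? |
|---|---|---|
| Abstract, Analysis | age, sex, socioeconomic status, medication | no |
| Section 4.2, confounders | the same four, as examples | no |
| Section 4.2, alpha-diversity and PERMANOVA | medication | no |
| Section 2.3, matching of B to A | sex, age | no |
| Section 2.2.3, Group C | diagnosis, age range | no |

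**3. Size of a city bias, A versus C.** The documents give neither the city mix nor the difference between cities, so both inputs are assumptions.

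Bias = (difference in city share between groups) × (outcome difference between cities)

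- Low end: 0.20 × 0.05 = 0.01, or 1 percentage point.
- High end: 0.40 × 0.15 = 0.06, or 6 percentage points.
- No imbalance: 0, whatever the difference between cities.

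**4. What that does to a test.** Take 100 versus 100, no true group effect, average prevalence 0.37 and a nominal two-sided level of 0.05. At the high end the expected prevalences are 0.40 and 0.34. The standard error is √(0.40 × 0.60/100 + 0.34 × 0.66/100) = 0.068, and 0.06 / 0.068 = 0.88. The rejection probability is Φ(0.88 − 1.96) + Φ(−0.88 − 1.96) = 0.14. At the low end the same calculation gives 0.052.

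**5. A versus pooled B and C.** If B has the same city mix as A, and B and C have 100 children each, the imbalance against the pool is half that against C. The bias becomes 0.5 to 3 percentage points. With 100 versus 200, the rejection probability is 0.051 to 0.08.

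**6. Test setting.** Sections 3.5.4 to 3.5.4.2 fix much of the test: wired headphones, audio-normalised video, a 105 dB pulse of 50 ms, and set trial numbers. Percent PPI is a ratio to the child's own pulse-alone trials, and short-term habituation is a change within the child, so a setting effect that scales all responses partly cancels. Postural sway, headphone touching and time out of frame (section 3.5.4.3) have no such protection. The documents give no accommodation rate for any group and no effect of setting on any measure, so no bias can be sized from them.

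**The case against.** **This is left to the analysis plan.** The article is condensed, section 4.2 introduces the confounders as examples, and sensitivity analyses are promised. That leaves room to add city. But the abstract states its list without that qualifier, section 4.2 goes as far as naming the microbiota covariate, and city appears in none of these places. Adding it is a specific change to a stated model.

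**City is probably balanced.** For A versus B this largely stands, because Group B follows the families of Group A. A reader might infer that city bias threatens the 20-point comparison on which the study is sized; the documents do not support that. For Group C the imbalance is unknown, neither shown nor excluded.

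**Socioeconomic adjustment already covers it.** It may absorb part of a city effect, but the six dimensions in section 3.5.1 do not include city or ethnicity.

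**City is missing from the nesting.** This is not a defect. Two cities are too few to estimate a random level.

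**Setting should be in the main sensorimotor models.** A reader might infer from sections 2.4 and 3.7 that autistic children are tested under non-standard conditions and that the sensorimotor comparison must be adjusted for this. The text does not go that far. The ethics wording concerns comfort during data collection generally and does not say that the acoustic stimuli change. Group C includes children with intellectual, hyperkinetic and emotional disorders, for whom requests may be just as common. If accommodation does follow from autistic sensory reactivity, it is a consequence of the condition being compared. Adjusting for it could remove real differences, and keeping only standard sessions could drop the most reactive children.

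**Conclusion.** The point holds for city as a fixed-effect covariate. The stated models and matching leave out a known, recorded factor that the article itself associates with population differences, and nothing in the design balances it for Group C. The contrasts exposed are A versus C and A versus the pooled non-autistic children, for diet, nutritional status and microbiota.

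The size is unknown. The 1 to 6 percentage points for A versus C rest wholly on an assumed 20 to 40 point imbalance and a 5 to 15 point difference between cities. With a balanced mix the bias is nil.

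For test setting, the documents support only the need to record place and accommodation and to examine them in a sensitivity analysis. They do not show a biased sensorimotor comparison, and they do not justify accommodation as a covariate in the primary sensorimotor models.

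**What to change.** 1. Add city (Quito or Riobamba) as a fixed effect in every group model and as a term in PERMANOVA. Do not model it as a random level.
2. Report the city mix for Groups A, B and C, and aim for a similar Quito-to-Riobamba mix in Group C where recruitment allows.
3. At each neurobehavioural session, record the place (home, centre or other) and whether any accommodation was made. Report both by group.
4. Use these two items only in a sensitivity analysis of PPI, habituation and the behaviour measures, read beside the primary city-adjusted result. Leave accommodation out of the primary sensorimotor models. No accommodation is withdrawn from any child.

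**Cost.** City takes one degree of freedom and is known for every child. The session record is two short items in REDCap. City can be added at analysis, but session conditions are best recorded at the visit, so items 2 and 3 belong within the planned collection period (fourth trimester of 2025 to fourth trimester of 2026). Aligning the city mix of Group C may slow its recruitment somewhat, which is why item 2 is worded as an aim.

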**Ethics and dissemination:**

The study has been approved by the Escuela Superior Politécnica de Chimborazo Ethics Committee (Ref: IO-01-CEISH-ESPOCH-2025). All participants will receive personalized nutritional counseling. Findings will be disseminated through peer-reviewed open-access publications, scientific conferences, and community workshops.

## Introduction

1

Autism is a neurodevelopmental condition characterized by two core diagnostic features, as defined by the Diagnostic and Statistical Manual of Mental Disorders (DSM-5): i) persistent deficits in social communication and interaction, manifesting as impairments in emotional reciprocity, verbal and nonverbal communication, and developing and maintaining relationships; and ii) restricted, repetitive patterns of behavior, interests, or activities, alongside cognitive inflexibility (1). These symptoms typically emerge in early childhood and cause significant functional impairment across social, occupational, and educational domains (2). In Ecuador, the estimated prevalence of autism is 682.70 cases per 100,000 individuals (3).

Although behavioral and cognitive impairments dominate autistic symptomatology, concomitant conditions such as malnutrition are prevalent. For example, studies indicate that overweight affects up to 35% and undernutrition up 20% of autistic children (3). Furthermore, autistic individuals are at higher risk of malnutrition, whether underweight, overweight, or obese, compared to non-autistic (NA) peers (4, 5). A critical driver of these disparities is sensorimotor integration differences (SMD), which alters responses to sensory stimuli (e.g., tactile, auditory, gustatory) in 69–95% of autistic individuals (6, 7).

Beyond food-related sensitivities (e.g., aversion to specific smells, tastes, textures), SMD contributes to malnutrition by underpinning core autistic traits including stereotypical behaviors, reduced behavioral flexibility, hyper- or hypo-reactivity, and anxiety. These traits lead to feeding problems such as food neophobia, heightened food selectivity, pica, and rumination (8). Consequently, individuals may suffer from deficiencies in essential nutrients like protein, iron, and vitamins, while consuming excessive amounts of polyunsaturated fats compared to their NA peers (8, 9). Such nutritional imbalances can further worsen core autistic symptoms and increase the risk of chronic conditions later in life (3, 10).

Restricted dietary patterns associated with SMD also impact the diversity, composition, and functionality of the gut microbiota (GM). Autistic children often show increased levels of taxa such as *Bacteroides*, *Parabacteroides*, *Clostridium*, *Faecalibacterium*, and *Phascolarctobacterium* and reduced levels of *Coprococcus* and *Bifidobacterium* (11, 12). Recent evidence further shows that microbial profiles vary with nutritional status (12). Among children with excess weight, those with autism have lower levels of *Roseburia* and *Faecalibacterium* and higher levels of *Eubacterium* and *Flavonifractor* than their NA peers (12). These dysbiotic shifts disrupt microbial balance, affecting the production of key microbial metabolites, including short-chain fatty acids (e.g., butyrate, acetate, propionate), neurotransmitters (e.g., gamma-aminobutyric acid), and vitamins.

Altered availability of these compounds may worsen autistic-related cognitive and behavioral symptoms by impairing the function of the gut-brain axis (13). For example, decreased levels of short-chain fatty acids have been linked to dysregulated serotonin signaling, which is often correlated with symptom severity (14). Furthermore, the increased prevalence of pathogenic bacteria associated with dysbiosis has been implicated in intestinal inflammation and hyperpermeability, which is referred to as “leaky gut” (15). These conditions can facilitate the translocation of bacterial and fungal harmful metabolites into the bloodstream and, later, into the central nervous system, thus further contributing to autistic symptomatology (16).

A major limitation in understanding the SMD-nutrition-microbiota relationship has been the reliance on caregiver-reported SMD assessments, such as the Short Sensory Profile (SSP). While instruments like the SSP have been extensively used in autism research, they remain subjective measures that may be influenced by caregiver perception, cultural context, and socioeconomic factors (17, 18). Moreover, their performance in non-Western populations has not been thoroughly evaluated. Neurometric tools such as pre-pulse inhibition of the startle response (PPI), offer an objective alternative for measuring sensorimotor assessment in autistic cohorts (19, 20). Innovations, such as a smartphone-based tool that enables accessible, non-invasive at-home neurobehavioral assessments, can provide standardized tests for measuring sensory gating and adaptation through the assessment of PPI and startle habituation (SH), as well as general sensorimotor behaviors (21, 22).

Therefore, we hypothesize that SMD in autistic children is associated with imbalanced dietary patterns, leading to malnutrition and changes in GM diversity and composition. These physiological alterations may collectively exacerbate autistic symptom severity, which in turn could further intensify SMD and feeding difficulties, establishing a self-perpetuating cycle of worsening symptoms and malnutrition. Our main objective is to investigate the relationships between SMD, dietary patterns, nutritional status and GM characteristics in autistic children compared to NA peers. Specifically, the study will (1): Compare dietary patterns and nutritional status between autistic children and NA peers (2). Assess differences in the GM (diversity, composition) between autistic children and NA peers (3). Quantify SMD by assessing PPI and SH and compare profiles across autistic children and NA peers (4). Examine associations between SMD, dietary patterns, nutritional status, GM profiles, and autistic symptom severity (5). Explore whether SMD mediates the relationship between autism and adverse nutritional/GM outcomes.

